The main objective of this prospective cohort study is to observe the recovery (or lack thereof) of maternal hypertension from week 2 to week 12 after a pregnancy affected by new onset of hypertension and identify the prevalence of persistent postpartum hypertension in this cohort of women. A secondary objective will be to assess the accuracy of HBPM in comparison with ABPM to inform if HBPM can be used as an alternative method for diagnosing hypertension in the postpartum period. Other outcomes of interest will include women’s self-reporting of their 6-week to 8-week GP postnatal review, their perceived risk of developing CVD associated with HDP, their emotional well-being and their views on HBPM and ABPM. These objectives will be assessed via online questionnaires distributed at 8 and 12 weeks post partum, respectively. In addition, healthcare professionals involved in the postnatal care of women with HDP will receive an online questionnaire assessing their knowledge on HDP and associated CVD risk.

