### Sample size

To obtain an accurate estimate of persistent hypertension rate after birth, a sample size of 263 women with a history of HDP are required. The target sample size is 300 women to compensate for study withdrawal and incomplete BP data. This is based on the anticipated rate of persistent postpartum hypertension of approximately 20% and the corresponding width of 95% CI to be 10% as desired level of precision, with 80% probability of achieving such precision. Considerations were also given to the sample size required to assess agreement between HBPM and ABPM.

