### Data analysis

#### Objective 1: to identify which BP will be used to calculate the rate of persistent hypertension at 12 weeks postpartum

The first and second BP readings will be compared with the third reading to assess if they vary by >10/5 mm Hg. The mean or median of all BPs will be used if no significance is found or the third BP reading will be used for interpretation if there is a significant difference (>10/5 mm Hg) between BPs. The BP taken at three time periods (morning, midday and evening) will also be analysed to assess if findings vary significantly by >10/5 mm Hg. If no significance is found, the mean or median BP readings for the day will be calculated and used for further analysis. If significant difference found, each time period will be compared with daytime ABPM to see which time point mostly correlates with daytime ABPM. This will be analysed using one sample t-test of the difference and intraclass correlation co-efficient (ICC).

Using descriptive statistics, HBPM readings for participants (not taking antihypertensive medication) will be categorised as per European Society of Cardiology guidelines^21^ into:

Prehypertensive (BP ≥130–134/80–84 mm Hg)Hypertensive (BP ≥135–139/85–89 mm Hg)Normotensive (BP <130/80 mm Hg)

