#### Objective 3: to assess the rate of hypertension over the postpartum period (weeks 2–12)

Using descriptive statistics, hypertension rates will be categorised under normotensive (<130/80 mm Hg), prehypertensive (130–135/80–85 mm Hg) or hypertensive (>135/85 mm Hg) at 2-week intervals post birth until 12 weeks postpartum. Univariate and multivariable logistic regression will be used to study what variables are associated with persistent postpartum hypertension at 12 weeks postpartum.

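### Objectives 1 and 3 define the hypertensive category differently for the same 12-week rate: one prints a cap at 139/89 and includes exactly 135/85, the other has no cap and excludes it

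*Protocol article*

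**What the plan says.** The Introduction sets the main objective as observing recovery from week 2 to week 12 and to "identify the prevalence of persistent postpartum hypertension in this cohort of women". The Sample size section plans around a rate of about 20%, with a 95% confidence interval 10 points wide.

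Two paragraphs under Data analysis then define the categories.

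- **Objective 1** is headed "to identify which BP will be used to calculate the rate of persistent hypertension at 12 weeks postpartum". It gives "Normotensive (BP <130/80 mm Hg", "Prehypertensive (BP ≥130–134/80–84 mm Hg" and "Hypertensive (BP ≥135–139/85–89 mm Hg", citing a cardiology guideline. It restricts the exercise: "HBPM readings for participants (not taking antihypertensive medication) will be categorised".
- **Objective 3** covers the rate at two-week intervals up to week 12. It uses the same normotensive limit, then "prehypertensive (130–135/80–85 mm Hg) or hypertensive (>135/85 mm Hg". It mentions no restriction by medication. The logistic regression for persistent hypertension at 12 weeks stands in this paragraph.

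**The concern.** The same woman, with the same week-12 readings, can be classified differently depending on which paragraph the analyst follows. The 12-week rate is what the study was sized to estimate, so its definition should be unique and fixed before the data are seen. With two definitions in print, the choice between them could be made after the results are known, and a reader of the final report could not tell which one had been planned.

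Three differences matter: the printed upper limit, the treatment of a value exactly on the boundary, and the population classified.

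**Working it through.** **1. The plan's own figure.** The sample size is not in dispute. Take p = 0.20, a 95% interval no wider than 0.10, and 80% probability of achieving that width. With the Wilson interval the exact binomial assurance is 0.786 at n = 262 and 0.819 at n = 263, so 263 is reproduced. The planned precision is ±5 points around 20%, which is the yardstick below.

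**2. The two lists side by side.**

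| Home value (mm Hg) | Objective 1 | Objective 3 |
|---|---|---|
| 125/75 | normotensive | normotensive |
| 132/82 | prehypertensive | prehypertensive |
| exactly 135/85 | hypertensive | prehypertensive |
| 137/87 | hypertensive | hypertensive |
| 145/95 | no category, read literally | hypertensive |
| any value, woman on antihypertensives | not classified | no restriction stated |

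The lists agree except on the third, fifth and sixth rows. The ≥ sign before a closed range in Objective 1 is also at odds with itself: the sign says open-ended, the range says closed.

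**3. Size of the cap and boundary differences (illustration only).** The documents give no distribution of blood pressure. Assumptions:

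- Systolic (S) and diastolic (D) values are bivariate normal, SD 10/8 or 12/9, correlation r = 0.6 or 0.7.
- Either component is enough to count. The documents do not state this.
- The planned 20% refers to P(S ≥ 135 or D ≥ 85). The Sample size section does not say this either.
- One constraint cannot fix two means, so the systolic mean is varied from 112 to 124 and the diastolic mean solved to give 20%.

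Formulas:

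- Literal capped rate = 0.20 − P(S ≥ 140 or D ≥ 90).
- Boundary shift on whole numbers = P(S ≥ 134.5 or D ≥ 84.5) − P(S ≥ 135.5 or D ≥ 85.5), that is, ≥135/85 minus >135/85 after rounding.

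| SD, r | Means | P(≥140 or ≥90) | Share of the 20% | Capped rate | Rate with ≥ | Rate with > | Shift |
|---|---|---|---|---|---|---|---|
| 10/8, 0.6 | 112/78.2 | 7.1% | 35.5% | 12.9% | 21.8% | 18.3% | 3.5 |
| 10/8, 0.7 | 124/76.1 | 7.7% | 38.7% | 12.3% | 21.7% | 18.4% | 3.3 |
| 12/9, 0.6 | 112/77.2 | 8.1% | 40.6% | 11.9% | 21.6% | 18.5% | 3.1 |
| 12/9, 0.7 | 124/71.7 | 9.8% | 49.0% | 10.2% | 21.3% | 18.7% | 2.6 |

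Over the whole grid the capped rate is 10–13%, a fall of 7–10 points, which exceeds the planned ±5. The boundary shift is about 3 points, inside ±5 but not negligible. On unrounded means of many readings almost no one sits exactly on 135 or 85, so the shift nearly disappears. Objective 1 leaves open whether a mean, a median or the third reading is used, and the last of these is a whole number.

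**4. The medication difference.** Let t be the share of women on treatment at week 12, and h_u and h_t the hypertensive proportions among untreated and treated women. Objective 1 estimates h_u. Objective 3, with no restriction, estimates (1 − t)h_u + t·h_t. The gap is t(h_t − h_u). The documents give none of these quantities, so no number is offered.

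**The case against.** The strongest reply is that the cap is a slip of the pen. Objective 1 puts ≥ before the range, Objective 3 gives the category without a limit, and hardly any analyst would leave women at 140/90 or above out of a hypertension rate. That is probably right. A reader might infer that the most hypertensive women will drop out of the result. The documents do not support that as a forecast; 10–13% is what the literal text gives, not a likely published figure. The boundary and population differences remain when the cap is removed.

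A second reply concerns reach, and it stands. A reader might infer that the faulty band drives every later analysis. The logistic regression sits in Objective 3, beside the uncapped definition. Objective 2 (kappa, sensitivity, specificity, McNemar's test) does not say that it uses the Objective 1 bands, and it plans to vary the home threshold.

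A third reply concerns discordant pairs such as 128/87. Neither list says whether both components or either one must meet the limit. One might infer that many women are left unclassified. But that follows only if both must match, which neither paragraph states. The omission also affects both paragraphs equally, so it creates no conflict between them, and a condensed article may leave it to the full protocol. Likewise, the space between 134 and 135 in Objective 1 is ordinary whole-number notation. Neither is counted here.

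**Conclusion.** The conflict is in the printed text and needs no outside source. Objective 1 and Objective 3 give different definitions of hypertensive for the same 12-week home blood pressure rate. They differ on the upper limit, on a value of exactly 135/85, and on whether women taking antihypertensives are classified.

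The two sizes, 10–13% against 20% for a literal cap and about 3 points for the boundary on whole-number values, rest on the assumed normal distribution, the either-component rule and the calibration to 20%. They show that the wording can matter at the scale of the planned precision; they are not estimates for this cohort. The medication difference cannot be sized. Because the cap is probably unintended and the correction is simple, this is a should-fix and not a flaw in the design or the sample size.

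**What to change.** Reconcile the two paragraphs into one analysis classification and refer to it from both objectives. It should:

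- be exhaustive and mutually exclusive, with no upper cap on the hypertensive category;
- state one boundary, ≥ or >, chosen by the sponsor and consistent with the guideline it cites, with the prehypertensive band ending where the hypertensive band begins;
- apply the same stated rule to women taking antihypertensives in both objectives;
- say in the same sentence how systolic and diastolic values combine.

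This review does not propose which boundary or threshold is right. The cost is wording in two paragraphs; no new data, visits or change in sample size are needed. It should be settled before the week-12 data are analysed.

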#### Objective 2: to compare the accuracy of HBPM against ABPM (gold standard) at 12 weeks postpartum

Cohen’s kappa will be used to measure the agreement between HBPM and day ABPM in diagnosing hypertension phenotypes. HBPM will also be compared with night and 24 hours ABPM indices. Accuracy of HBPM will be assessed through sensitivity, specificity, positive and negative predictive values. HBPM will be compared with night and 24 hours ABPM indices to assess. Thresholds for diagnosing hypertension in HBPM will be adjusted to explore the optimal threshold using area under the receiver operating characteristic curve or kappa score. The McNemar’s test will be used to assess whether there is a systematic difference between the HBPM and ABPM for diagnosing hypertension. ICC will be used to check for agreement and Bland-Altman diagrams will also be used to check for random/systematic effects between HBPM and ABPM measurements.

#### Objective 3: to assess the rate of hypertension over the postpartum period (weeks 2–12)

Using descriptive statistics, hypertension rates will be categorised under normotensive (<130/80 mm Hg), prehypertensive (130–135/80–85 mm Hg) or hypertensive (>135/85 mm Hg) at 2-week intervals post birth until 12 weeks postpartum. Univariate and multivariable logistic regression will be used to study what variables are associated with persistent postpartum hypertension at 12 weeks postpartum.

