**Methods and analysis:**

This prospective cohort study design will ask approximately 300 participants to complete 3 days of home blood pressure monitoring every fortnight for 12 weeks postpartum and will culminate with a 24-hour episode of ambulatory blood pressure monitoring at 12 weeks postpartum. Women and healthcare professionals will complete questionnaires surrounding postpartum care for women who had HDP and knowledge of CVD risk. In addition, the relationship between hypertension and factors likely to influence outcomes such as severity of HDP, maternal age, body mass index and ethnicity will be analysed using logistic regression. Blood pressure and data from questionnaires will be analysed using descriptive statistics, with temporal stratification.

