**Trial registration number:**

NCT05137808.

Strengths and limitations of this studyThis is the first study to our knowledge exploring the recovery of blood pressure longitudinally in the immediate postpartum period after gestational hypertension.Home blood pressure monitoring will be compared against the gold standard; ambulatory blood pressure monitoring.Self-monitoring and reporting of blood pressure measurements by research participants may introduce the challenge of missing data.

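### The main aim is recovery from week 2 to week 12, but the stated analysis is separate fortnightly rates, which estimate neither within-woman recovery nor change over time

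*Protocol article*

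**What the plan says.** The aim is longitudinal. The Introduction gives the main objective as to "observe the recovery (or lack thereof) of maternal hypertension from week 2 to week 12", together with the prevalence of persistent hypertension. The strengths and limitations box claims novelty for "exploring the recovery of blood pressure longitudinally in the immediate postpartum period".

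The analysis stated for that course is cross-sectional at each session:

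- Data analysis, Objective 3: "Using descriptive statistics, hypertension rates will be categorised under normotensive", prehypertensive or hypertensive, "at 2-week intervals post birth until 12 weeks postpartum".
- Abstract, Methods and analysis: BP data will be "analysed using descriptive statistics, with temporal stratification".
- The only model, also under Objective 3, is univariate and multivariable logistic regression of "what variables are associated with persistent postpartum hypertension at 12 weeks postpartum".

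Three other statements bear on the point:

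- The strengths and limitations box warns: "Self-monitoring and reporting of blood pressure measurements by research participants may introduce the challenge of missing data".
- Sample size: "The target sample size is 300 women to compensate for study withdrawal and incomplete BP data", against 263 required.
- Objective 1 limits the categorisation of home readings to women not taking antihypertensives. Objective 3 does not repeat that limit.

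**The concern.** Recovery and persistence are properties of a woman followed over time. A series of six rates (weeks 2, 4, 6, 8, 10 and 12) is a property of the group at each session. The design measures the same women up to six times, but the stated analysis does not link one session to the next.

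The Introduction expects the results to show what share of women stay hypertensive across weeks 2 to 12, and whether more BP monitoring is needed between weeks 2 and 8. A group in which most affected women recover and others become hypertensive later raises a different monitoring question from a group in which the same women stay hypertensive throughout. The planned tables could look identical in both cases. A reader would also have no interval by which to judge whether a drop between two fortnights exceeds chance.

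**Working it through.** **1. The plan's own figure.** Inputs from Sample size: anticipated rate 20%, full 95% CI width 10 points, 80% probability of achieving that width.

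- Without the 80% condition: n = 1.96² × 0.20 × 0.80 / 0.05² = 245.9, so 246.
- With it: the smallest n for which P(width ≤ 0.10) ≥ 0.80 when X ~ Binomial(n, 0.20). The Wilson interval, with width 2z√(p(1−p)/n + z²/4n²)/(1 + z²/n), gives n = 263 (probability 0.819). Jeffreys also gives 263, and Wald gives 264.

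The 263 is reproduced. It sizes one proportion at one time, so it says nothing about precision for change over weeks 2 to 12.

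**2. What two separate rates leave open.** Assume complete data on 300 women, with 90 hypertensive at week 2 (30%, an assumption) and 60 at week 12 (the anticipated 20%). Let r be the number hypertensive at week 2 but not at week 12, and c the number hypertensive at week 12 but not at week 2. Then 90 − r + c = 60, so r − c = 30, with r anywhere from 30 to 90.

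| | Least turnover | Most turnover |
|---|---|---|
| Recovered, r | 30 | 90 |
| Newly hypertensive or relapsed, c | 0 | 60 |
| Recovery among the 90 | 30/90 = 33% | 90/90 = 100% |
| Hypertensive at both weeks, (90 − r)/300 | 60/300 = 20% | 0/300 = 0% |

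Both columns give the same two entries in the Objective 3 table: 30% and 20%.

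**3. The interval for change.** The fall is 10 points in both columns. For paired data, SE = √[(r + c) − (r − c)²/n]/n.

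- Least turnover: √(30 − 900/300)/300 = √27/300 = 0.0173; half-width 1.96 × 0.0173 = 3.4 points.
- Most turnover: √(150 − 900/300)/300 = √147/300 = 0.0404; half-width 1.96 × 0.0404 = 7.9 points.
- Treating the two rates as independent samples: √(0.30 × 0.70/300 + 0.20 × 0.80/300) = 0.0351; half-width 6.9 points.

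The correct interval needs r and c, which the separate rates do not supply.

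**4. Sensitivity to part-way stopping.** This shows only that direction depends on the assumption. Take a true rate of 30% at every session, and suppose 37 of 300 women (12.3%, the allowance implied by 300 − 263) have stopped by week 12.

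- Hypertensive women twice as likely to stop: the stopping probability for the others is 0.1233/(0.30 × 2 + 0.70) = 0.095, and for hypertensive women 0.190. Observed rate 0.30 × (1 − 0.190)/0.877 = 27.7%.
- Normotensive women twice as likely to stop: the probability for hypertensive women is 0.1233/(0.30 + 0.70 × 2) = 0.073. Observed rate 0.30 × (1 − 0.073)/0.877 = 31.7%.

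The ratios are assumed, and the article gives no rate of part-way stopping. Data collection also says the readings are uploaded when diaries and monitor come back at 12 weeks. A woman who never returns them may be absent from all six sessions, which shifts the level of every rate and not the trend.

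**The case against.** The strongest reply is that the descriptive choice fits the objective's own words. The protocol says it will observe recovery and identify prevalence, and Objective 3 is headed as a rate. Every participant enters with diagnosed new-onset hypertension, so the share still hypertensive at each fortnight describes recovery from a common start. Descriptive statistics also do not exclude a transition summary.

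Part of this stands. The serial rates are legitimate, should stay, and give the 12-week prevalence. But the stated course begins at week 2, when some women may already be normotensive, and the rates cannot separate failure to recover from relapse. A transition summary is compatible with the text but is not stated. The abstract and Objective 3 agree on the method, so this is a stated choice and not a detail lost in condensing.

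A reader might infer more:

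- *That the rates will cover only women who returned readings, so drop-out will pass for recovery.* The article gives neither denominators nor missing-data handling. A condensed article commonly leaves these to the full protocol, so the silence is no finding. A false trend would need stopping that grows over the weeks and is related to BP; neither is shown.
- *That a biased 12-week rate measures a false trend.* Bias in one rate at one session, under an assumed risk ratio, says nothing about slope.
- *That the regression has too few events per term or wrongly dichotomises BP.* The article does not fix the number of terms, and a binary 12-week status is the question it asks.

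**Conclusion.** The point holds as a mismatch between aim and stated method. Followed as written, the plan yields six descriptive rates and a week-12 regression, but no estimate of recovery or relapse and no interval for change. In the illustration, the same pair of rates fits recovery from 33% to 100% and a half-width for change from 3.4 to 7.9 points. That rests on an assumed 30% rate at week 2, the plan's 20% at week 12, and complete data, so the ambiguity exists before any reading is missing. The range marks arithmetical limits; it does not forecast turnover.

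Sensitivity to part-way stopping is a secondary and conditional reason to act. Its size and direction cannot be known from the article, and the conclusion does not depend on it.

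The antihypertensive restriction is a separate inconsistency in the text. If the Objective 1 limit applies at each session, the denominator changes as women start or stop treatment. If it does not, treated and untreated readings are mixed.

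**What to change.** 1. Keep the fortnightly descriptive tables and print the number of women contributing at each session.
2. Add a within-woman transition table, for example week-2 by week-12 status, with recovered, persistent and newly hypertensive women counted separately.
3. Add one repeated-measures analysis using all available sessions, with week as a categorical term. For hypertension status, use GEE, or a mixed logistic model with rates averaged over the woman effect so that they are population rates. For systolic and diastolic BP, use linear mixed models. Report change from week 2 with 95% CIs.
4. Reconcile Objectives 1 and 3 on women taking antihypertensives. State one analysis rule and apply it at every session, in the transition table and in the model.

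The cost is modest analysis time, with no new data, participant contact or change in sample size. The mixed models assume data missing at random given the observed readings and covariates. An unweighted GEE needs the stronger condition that missingness does not depend on earlier BP. Neither recovers information on a woman whose diary and monitor never come back.

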### Questionnaires

The questionnaires will be analysed to answer the remaining objectives:

The care provided to women at the postnatal GP review in terms of their HDP.Participants’ risk perception of CVD.Participants’ emotional well-being.Participants’ views on HBPM and ABPM.Clinicians’ knowledge on HDP and association with CVD development.

Categorical variables will be expressed as frequencies and percentages and continuous variables will be expressed as mean, median, SD and IQR. The data will be analysed and presented using descriptive statistics.

### Ethics and dissemination

This study was approved by London-West London & GTAC Research Ethics Committee. All participants will sign an informed consent form after taking time to read the participant information leaflet. There is a risk of identifying significant hypertension at home and all participants will be counselled on the actions to follow if this were to occur.

The results of this study will be distributed via peer-reviewed academic journals, educational maternity update events for clinicians involved in the care of postpartum women and presenting at conferences and relevant expert meetings. The PPI steering group will be involved in the creation of infographics for a lay audience which will be disseminated among their peer groups and social media platforms to increase the likelihood of key health promotion messages reaching women who have had a hypertensive disorder of pregnancy.
